#### Key Strategies of and Differences Between NH-CBT and the Active Control Treatment

##### NH-CBT

The NH-CBT program builds on the predictive coding theory of FNSD/PMD (20). It is assumed that participants' motor symptoms can be explained by a strong mental representation of their body or parts of their body as neurologically damaged or diseased. The key component of this treatment is to retrain participants' symptom processing and to reduce the strength of this mental representation. The following four key strategies of NH-CBT are essential to address the four basic treatment principles mentioned earlier:

To help participants to understand the role of their “priors” or beliefs as mechanisms causing their symptoms and to remind them about the neurological evidence for a lack of neurological damage or disease (i.e., what is not causing their symptoms), the concept of the “nocebo effect” is explained and used to inform a cognitive behavioral formulation which explains their symptoms. The psychoeducation component of NH-CBT shall provide the individual with a new, alternative belief (i.e., what is causing their symptoms).The movement retraining strategies are used in the sense of a behavioral experiment. They are essential to provide the participants with new and precise “motor input” to lower the precision and strength of their abnormal prior beliefs. The therapist and participant will continue reflecting on the change of “priors” and beliefs during the movement retraining as being the only possible mechanism behind any improvement.This process is video-recorded, and feedback is promptly given to the participant that any normalized movement is evidence confirming the nocebo explanation for their symptoms and disconfirming the presence of neurological damage.To divert participants' attention and to lower the precision-increasing effect on abnormal priors, they have to be distracted while they practice movements.

##### Supportive Counseling and Movement Retraining (Active Control Intervention)

The control intervention was designed to control for the non-specific effects of (a) education about symptoms, (b) emotional support from a therapist, and (c) movement retraining. For (a), the psychologist will reassure the participant that symptoms are not caused by structural damage or a degenerative process, however there will be no conversation about beliefs or expectations being an important factor in the development and maintenance of functional motor symptoms. The concept of a nocebo effect will not be mentioned. The psychologist will mainly repeat the explanation of FNSD/PMD by Stone (29) that will have already been provided by the neurologist during the initial neurological assessment. For (b) the psychologist will provide supportive counseling about the participants' symptoms and associated distress and everyday impact, and strategies to manage distress such as relaxation exercises. For (c), motor symptoms will be conceived of as learnt patterns of movement that are outside participants' control. The movement retraining will attempt to re-establish normal movement patterns, but without video feedback and distraction techniques.

The active control intervention will not address any of the key treatment strategies of NH-CBT. The active control intervention will differ from the NH-CBT regarding the following aspects:

It will not include any discussion of the concept of the “nocebo effect” or the role of beliefs as mechanisms of functional motor symptoms.The movement retraining will not be used in the sense of a behavioral experiment, but as a systematic attempt to re-establish normal movement.It will not involve any means of visual feedback.It will not use any engrossing, external distractors, such as music, video, video games, irrelevant conversation, or counting. The only redirecting of attention will involve a suggestion that the participant focus on a point in space, instead of on their bodies.

**Primary outcome measure**					
Physical functioning	Short Form-36 Health Questionnaire (SF-36), Physical Functioning subscale (39)	x	x	x	x
**Secondary outcome measures**					
**Somatic symptoms**					
Functional motor symptoms	Simplified Functional Movement Disorder Rating Scale (S-FMDRS)^*^ (30)	x	x	x	x
Fatigue	Short Form-36 Health Questionnaire (SF-36), Vitality subscale (39)	x	x	x	x
Somatic symptom severity	Patient Health Questionnaire-15 (PHQ-15)	x	x	x	x
**Illness consequences**					
Mobility	10 m-Walk Test^*^ (32)	x	x	x	x
	Functional Mobility Scale (FMS)^*^ (31)	x	x	x	x
Symptom disability	Modified Pain Disability Index (PDI) (41, 42)	x	x	x	x
Health-related quality of life	Short Form-36 Health Questionnaire (SF-36) (39)	x	x	x	x
Quality of Life	EuroQol-5D (EQ-5D-5L) (43)	x	x	x	x
Health care utilization (past 3 months)	Item 7 and 8 of the modified Client Service Receipt Inventory (CSRI) for chronic pain patients (44, 45)	x		x	
Health care utilization	Participants' electronic health records	x		x	
**Psychological features**					
Anxiety	Generalized Anxiety Scale-7 (GAD-7) (46)	x	x	x	x
Depression	Patient Health Questionnaire-9 (PHQ-9) (47)	x	x	x	x
Catastrophic thinking about symptoms	Symptom Catastrophizing Scale (SCS) (48)	x	x	x	x
Illness perception	Brief Illness Perception Questionnaire (BIPQ) (49)	x	x	x	x
Dissociation	Brief Dissociative Experiences Scale (B-DES) (50, 51)	x	x	x	x
**Participant satisfaction**					
Therapeutic alliance	Work Alliance Inventory—Short Form (WAI-SR) (52)		x		x
Participant's perception of change	Clinical Global Impression Scale of Improvement (CGI-I) (53)		x	x	x
**Adverse events**					
Adverse events in therapy	Inventory for the Assessment of Negative Effects of Psychotherapy (INEP) (54)		x		x
Adverse events in therapy	Severity Assessment Code rating for adverse event reporting (SAC)^†^(33)				

* *Blinded assessor rating*.

† *The SAC will be applied during the 8 weeks of NH-CBT in case of serious adverse events*.

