Participants have to understand the role of their “priors” or beliefs as the key mechanism behind their symptoms.It is essential to provide the participants with new and precise “motor input” to lower the precision and strength of their abnormal prior beliefs, to develop a new belief, and to help increase the precision and strength of this new belief.The precision of the new motor input can be further increased and the abnormal prior belief should be modified by promptly providing participants with visible feedback about their movements.Participants' attention has to be diverted to lower its precision-increasing effect on abnormal priors.

Richardson et al. (27) previously examined the effects of NH-CBT in a retrospective case series design without a control group. The authors examined the effect of the treatment protocol in 12 patients with either weakness/reduced mobility, or tremor, or non-epileptic seizures, or mixed symptoms. In seven of the 12 episodes a clinically reliable and significant change of the functional motor symptoms was reached.

The central aim of this RCT is to investigate if NH-CBT for participants with persistent functional motor symptoms is more effective in improving physical functioning (primary outcome) (hypothesis 1) and secondary outcomes (hypothesis 2) in comparison to an active control intervention at the end of therapy. We will also examine if treatment effects can be maintained over 8 weeks post-intervention (hypothesis 3). Participant characteristics at baseline will be investigated as moderator variables of the intervention effect on an exploratory basis.

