## Methods and Analysis

### Setting, Participant Recruitment, and Eligibility Criteria

The study will be conducted at the ISIS Centre, a rehabilitation ward of Wakari Hospital (Dunedin, New Zealand), where people with neurological conditions undergo outpatient and inpatient treatment. Participants will be referred by neurologists from the Neurology Department at Dunedin Public Hospital (Southern District Health Board). The ISIS Centre is part of the Southern District Health Board of New Zealand and covers the neurological rehabilitation of 7% of the country's population (~337,000 people).

The inclusion criteria will be:

Aged 18 or olderNew or returning patients presenting to the participating Neurology DepartmentDiagnostic investigations by a neurologist including the appropriate medical examination have been completed.Diagnostic investigations resulted in a diagnosis of FNSD with abnormal movement according to diagnostic criteria of DSM-5 (1) or of a PMD according to the diagnostic criteria by Gupta and Lang (2). Acute (<6 months) as well as persistent symptom presentations (≥6 months) will be accepted.The symptoms cause clinically significant distress or impairment in social, occupational, or other important areas of daily functioning.

Exclusion criteria will be:

Diagnosis of a complex regional pain syndrome, Dissociative Identity Disorder, or Posttraumatic Stress Disorder of high severity with significant dissociationSevere mental health disorder requiring inpatient mental health treatment or potentially affecting trial participation (e.g., suicidality, acute psychosis, active or extensive self-harm)Receiving concomitant psychological intervention that targets motor symptomsInitiation or change in regimen of psychopharmacotherapy at any time between 4 weeks before baseline assessment and the final follow-up assessmentPresence of significant physical trauma/comorbid health conditions (e.g., significant musculoskeletal injuries, severe respiratory illness) precluding participation in our movement retraining (we will include participants who are diagnosed neurological conditions, as long they have individual symptoms that are considered to have a high degree of certainty that they are functional)Low English language proficiencyInability to provide informed consent to participate in the trial

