The first part of the *psychological assessment* is a clinical interview where the principal investigator (MR) will provide individuals interested in participating with more detailed information about the study. We will explain to potential participants that we will offer them one of two treatments: one is conventional and more commonly used for individuals with FNSD, and has been found to be effective; and the other is new, and we are yet to establish evidence of its efficacy. Participants will be blinded to details of the content and proposed mechanisms of NH-CBT and the control treatment, and to differences between both treatments. They will only be informed that the core component of both treatments will be movement retraining, delivered by a rehabilitation professional. During the first part of the psychological assessment we will assess whether individuals meet all eligibility criteria and will ask them to give written consent to participate. In the second part, an assessor who is independent of this study and trained in applying the assessment tools will do the *baseline assessment*. The research assistant will do the Simplified Functional Movement Disorder Rating Scale (S-FMDRS) (30), the Functional Mobility Scale (FMS) (31) and the 10 m-Walk Test (32) with the participant. A physiotherapist will be present to ensure the safety of the participant. Participants will complete a baseline questionnaire including questions about demographic variables and all other outcome measures (see *Outcomes and Assessments*).

Participants will then be randomly assigned to receive either NH-CBT or the active control treatment over the following 8 weeks. At the end of the intervention period (*8-week follow-up*) participants will attend another assessment with an independent, blinded assessor and will complete all outcome measures. Sixteen weeks after baseline, participants from both groups will complete all outcome measures again (*16-week follow-up*). At that point, participants in the control group who have not achieved symptom remission will be offered NH-CBT and will be asked to complete a final questionnaire after 8 weeks of treatment (*24-week follow-up*).

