	*NH-CBT relapse prevention (1 session)*: The treatment cycle is taken as far as possible in the final session. Therapist and participant collaboratively set a final movement goal that is as high as the participant wishes. The participant then tries to achieve it. The second part of the relapse prevention stage gives clear advice to people about what to do if symptoms re-emerge in future. For each individual person, a personalized behavioral experiment is devised that will prove to participants that their most feared neurological event is not happening. This experiment involves them reminding themselves that minor transient symptom, often referred to as “glitches”, are harmless and are just the subconscious expressing a momentary doubt via a nocebo effect.	*Control relapse prevention (1 session)*A self-management plan is introduced to the participant, including a summary of useful strategies that help to normalize movement, activity plans to address boom and bust patterns and how to progress activity, future goals, and what to do on difficult days and during periods of symptom exacerbation. Therapists are instructed to avoid making any suggestions that state or imply the role of illness beliefs.
5. Who provided	*Neurological assessment:* All neurologists involved in this trial will be employed on consultant level. They will receive training from the PI (MR) in person or by telephone. They will have been given suggestions by Stone (29) of how to explain FNSD/PMD to participants.	
	*NH-CBT psychoeducation*: clinical psychologist (PI: MR)	*Psychological input and supportive counseling*: clinical psychologist (other than PI)
	*NH-CBT movement retraining*: licensed rehabilitation professional (physiotherapist, occupational therapist, rehabilitation assistant), with a physiotherapist always having a role in developing the treatment plan (including safety management plan) and having oversight of the physical elements of the treatment	*Control movement retraining*: licensed rehabilitation professional (physiotherapist, occupational therapist, rehabilitation assistant), with a physiotherapist always having a role in developing the treatment plan (including safety management plan) and having oversight of the physical elements of the treatment

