#### Statistical Analysis

Analyses will be based on intention-to-treat principles and will be carried out at the end of the last follow-up assessment. We will apply a linear mixed-effect model with baseline adjustment with main effects (fixed effect) for time (level 1, contrasts to baseline at 8- and 16-week follow-up) and group (level 2), group-by-time cross-level interaction term (8- and 16-week follow-up), and a generalized covariance matrix to account for dependency among observations. In order to deal with missing values, maximum likelihood estimation will be applied. Patterns of missing values will be assumed to be random. The outcomes of interest will be the group-by-time interaction at week 8 (hypothesis 1 and 2), and at week 16 (hypothesis 3). Effect sizes (Cohen's d) with 95% CI of changes between baseline and 8- and 16-week follow-up, as well as of between-group differences at 8- and 16-week follow-up will be investigated. Further sensitivity analyses will be conducted depending on the dropout rates and pattern of dropout reasons. For this purpose the linear mixed-effect models described above will be rerun for defined subgroups of the total sample (e.g., for participants with complete datasets only). To test for moderation (exploratory research question) we will add the moderator variable to the linear mixed-effect model described above (level 1: time; level 2: group) and will analyze a 3-level interaction. A significance level of 5% will apply to all analyses. Statistical analyses will be conducted with SPSS.

A limitation of group analyses is that it provides no information about the relative proportions of participants who did or did not respond to a treatment, which is based on a set standard. In accordance with recommendations by the Initiative on Methods, Measurement, and Pain Assessment in Clinical Trials (58), we will compare the distribution of participants with an improvement of at least 30 or 50%, no change, or deterioration on the primary outcome between the study groups with χ^2^-tests. Groups will be compared regarding adverse therapy effects, measured with the Inventory for the Assessment of Negative Effects of Psychotherapy, with independent sample *t*-tests and χ^2^-tests. To assess interrater reliability of the treatment fidelity ratings, intraclass coefficients (two-way random model with measure of agreement) for each item will be computed.

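### Arms are compared for benefit at weeks 8 and 16, but adverse-event collection is scheduled only for the therapy weeks

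*Protocol article*

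**What the plan says.** **Benefit.** The Introduction sets the maintenance aim: "We will also examine if treatment effects can be maintained over 8 weeks post-intervention (hypothesis 3"). Statistical Analysis tests it between arms: "The outcomes of interest will be the group-by-time interaction at week 8 (hypothesis 1 and 2), and at week 16 (hypothesis 3").

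**Harm questionnaire.** Under Adverse events, Table 2 lists the "Inventory for the Assessment of Negative Effects of Psychotherapy (INEP) (54") with marks at the 8-week and 24-week follow-ups and none at week 16. Study Design and Procedure, however, says: "Sixteen weeks after baseline, participants from both groups will complete all outcome measures again". The same section describes who reaches week 24: "participants in the control group who have not achieved symptom remission will be offered NH-CBT and will be asked to complete a final questionnaire". That questionnaire comes once the delayed treatment has been given. Statistical Analysis plans a between-group comparison of the inventory by t-tests and χ² tests and names no time point.

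**Serious adverse events.** Data and Patients' Safety Monitoring has the therapist complete the SAC rating and contact the principal investigator within 24 hours. It does not distinguish between arms. The Table 2 footnote ties use of the SAC to the 8-week NH-CBT period, and no time point is marked in the SAC row. The Abstract says adverse events are monitored across sessions. Under Interventions, sessions run over 8 weeks in both arms.

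**The concern.** A claim that benefit lasts to week 16 should be accompanied by a harm comparison over the same period. Here the randomised comparison of benefit covers 16 weeks and the scheduled collection of adverse events covers 8. If NH-CBT is reported as superior at week 16, the report will have no between-arm adverse-event data for the second half of that period.

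The data safety and monitoring board is also affected. Its decisions on harm rest on serious adverse events that reach it. For an event in week 12, say, the article states no collection point and no reporting route.

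A second problem sits in the SAC footnote. Read literally it names NH-CBT only, so the control arm has no SAC rating even in weeks 0 to 8. That conflicts with the safety-monitoring section. If staff followed the footnote, the arms would be monitored unequally and any comparison of serious events would be biased by design.

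**Working it through.** This is a check of schedules, so the main step sets the stated windows side by side for the randomised period.

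| Item | Weeks 0–8 | Weeks 8–16 | After week 16 |
|---|---|---|---|
| Benefit compared between arms | Yes, at week 8 | Yes, at week 16 | No |
| Negative-effects inventory (Table 2) | Week 8, both arms | Blank | Week 24, non-remitted controls after delayed NH-CBT |
| Session-based monitoring (Abstract, Interventions) | Both arms | No sessions scheduled | Delayed NH-CBT only |
| SAC (footnote, read literally) | NH-CBT arm only | Neither arm | Delayed NH-CBT, if the footnote extends to it |
| SAC (safety-monitoring section) | Both arms, via the therapist | No window stated | No window stated |

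**Share of randomised follow-up.** (16 − 8) / 16 = 0.50. With the planned 172 participants, 172 × 8 = 1,376 of 172 × 16 = 2,752 person-weeks, before dropout. This is the same 50% on another scale. The sample size plays no other part in the point.

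**How many events could fall there.** The documents give no event rate, so this is an assumption shown over a range. With 172 / 2 = 86 per arm and a risk p per participant in weeks 8 to 16, the expected number with an event is 86p and the chance of at least one is 1 − (1 − p)^86:

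- p = 1%: 0.86 expected; chance 0.58
- p = 2%: 1.72 expected; chance 0.82
- p = 5%: 4.3 expected; chance 0.99
- p = 10%: 8.6 expected; chance above 0.99

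Even a low risk would probably produce at least one event per arm in the period without scheduled collection.

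**What is recorded at week 16.** Table 2 marks the SF-36, the S-FMDRS, the walk test, the FMS, the PHQ-9, the GAD-7 and the CGI-I at week 16. It also marks service-use items and "Participants' electronic health records". The last two are listed as health care utilisation, and Outcomes and Assessments describes them as cost signals. The service-use items look back 3 months, about 13 weeks, so at week 16 they reach back to about week 3 and do not isolate weeks 8 to 16.

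**Early finishers.** Table 1, item 8, allows therapy to end early under stated conditions, and therapy dropouts are encouraged to stay in follow-up. For these participants the therapist route can close before week 8, although the week-8 inventory still applies.

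**The case against.** The timing of the inventory can be defended. Table 2 labels it as covering adverse events in therapy, and it follows the pattern of the therapeutic-alliance measure: once at the end of each treatment period. The phrase about all outcome measures at week 16 may be shorthand, because the same section uses it for week 8, where the service-use items and health records are blank. That weakens the mismatch as evidence of a lost assessment. It does not supply harm data for weeks 8 to 16, and the two places still need to agree.

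It can also be said that a journal article leaves reporting windows and routes to the full protocol. That is fair for what the article does not mention. It does not cover the SAC footnote, which states a window and an arm.

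Three stronger readings are tempting and are not supported:

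- A reader might infer that harms after week 8 go unmeasured and that late deterioration would be missed. The week-16 scales, several of them rated by a blinded assessor, would show worsening in function, movement, mood and anxiety. Statistical Analysis also compares deterioration on the primary outcome between groups, though without a time point. The accurate statement is that events are not collected as adverse events.
- A reader might infer that the therapist is the only permitted reporter. The article names no other route, but it does not exclude one.
- A reader might set the relapse-prevention advice that minor transient symptoms "are harmless and are just the subconscious expressing a momentary doubt via a nocebo effect" against the eligibility note that "we will include participants who are diagnosed neurological conditions", and see a contradiction. The wording does not show one. The advice concerns minor, passing symptoms, and the eligibility note requires high certainty that the individual symptoms are functional.

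**Conclusion.** The point holds as a mismatch of schedules. Benefit is compared between the randomised arms at weeks 8 and 16, while adverse events are scheduled for collection as such only in the 8 therapy weeks. The gap is 8 of 16 randomised weeks in both arms. A maintenance claim under hypothesis 3 would have no matching between-arm adverse-event comparison for weeks 8 to 16. Separately, the SAC footnote and the safety-monitoring section disagree on whether the control arm is covered.

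This does not touch the primary outcome, its analysis or the sample size. It is worth correcting because the gap is stated in the schedule and is cheap to close. The conclusion assumes that Table 2 is the operative schedule and that the full protocol, not shown, does not set a different reporting window. The number of events affected is unknown; the range given rests on assumed rates.

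**What to change.** 1. In Table 2, mark the negative-effects inventory at week 16 for both arms. For this measure, that also brings the table into line with Study Design and Procedure. In Statistical Analysis, name weeks 8 and 16 as the time points for its between-group comparison.
2. Correct the SAC footnote to cover both arms through week 16, consistently with Data and Patients' Safety Monitoring.
3. Use the week-16 health-record extraction already scheduled for utilisation to list hospital admissions, injuries and new or worsened neurological diagnoses since week 8. Report these by arm to the data safety and monitoring board. The documents do not show that a psychotherapy negative-effects inventory would pick up injuries or diagnoses, so this step complements the first.

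The cost is one more questionnaire at an existing assessment and a few extra fields in a planned record review. No new visit is needed and the sample size is unchanged. The downside is slightly more participant burden and review work.

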## Abstract

**Introduction:** Functional Neurological Symptom Disorders (FNSD) are associated with high levels of disability and immense direct and indirect health costs. An innovative interdisciplinary rehabilitation approach for individuals with functional neurological symptoms of motor type–Nocebo-Hypothesis Cognitive Behavioral Therapy (NH-CBT)—combines CBT and movement retraining with video feedback embedded in a comprehensive explanatory model of the etiology of FNSD.

**Methods:** This protocol describes the development and implementation of a phase II, parallel group, randomized controlled trial with blinded outcome assessors to compare the efficacy of NH-CBT with an active control condition (supportive counseling and movement retraining). Individuals meeting diagnostic criteria of an FNSD or psychogenic movement disorder will be randomly assigned to one of the 8-week interventions. Self-report scales of motor and other physical symptoms, symptom-related psychological variables, and assessor ratings of participants' mobility will be administered at baseline, and at 8- and 16-week follow-up. Adverse events will be monitored across all sessions and therapeutic alliance will be measured at the end of therapy. The primary statistical analysis will test the hypothesis that NH-CBT is more effective than the control intervention at the 8-week follow-up.

**Discussion:** The therapeutic strategies of NH-CBT are theory-driven by assumptions of the predictive coding model of the etiology of FNSD. Strengths and limitations of this trial will be discussed.

**Trial registration**: Australian New Zealand Clinical Trials Registry (ANZCTR; identifier: ACTRN12620000550909).

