
### Data and Patients' Safety Monitoring

Participants with any type of neurological diagnosis with a range of associated physical disabilities (e.g., weakness, balance difficulties) are at some risk of falling. According to clinical observations, people with FNSD/PMD are at lower risk of injury than people with neurological damage (16). However, there are still some incidents with this group. Treatment necessarily involves taking managed risks whilst ensuring safety, using management strategies and mobility aids. All trial participants will be assessed by a physiotherapist as they start the movement retraining part of the treatment (see *Interventions*) and throughout the treatment if needed, to ensure adequate steps are taken to ensure safety. In the case of serious adverse events (SAE) the Severity Assessment Code (SAC) rating for adverse event reporting (33) will be completed by the therapist. The study therapist has to contact the principal investigator (MR) within 24 h after the event. The PI will not be blinded to the result of the randomization and will therefore be able to decide if the SAE was a serious adverse reaction to the trial treatment.

In order to monitor and supervise the progress of the trial and SAEs associated with the trial treatment, an independent Data Safety and Monitoring Board will be involved, including a psychiatrist, a statistician, a manager of the ISIS Centre and a person who was formerly treated for FNSD at ISIS as a stakeholder of patients' interests. The DSMB will meet on a regular basis and will make final decisions to terminate the trial prematurely for harm, based on their monitoring and evaluation of SAE attributed to our treatment. The SAC rating for adverse event reporting allows for differentiation of four levels of severity of adverse events (34). In the case of severe and major events (SAC 1 and 2), the trial would have to be suspended with immediate effect pending investigation. The DSMB will discuss SAC 3 and 4 events (minor to moderate events), how they relate to our treatment and how they will influence the further course of this trial. The DSMB will also make final decisions to terminate the trial prematurely for benefit, based on stopping rules and interim analyses described below (see *Sample size, power calculations, and interim analyses*).

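### The Table 2 footnote ties the SAC rating to NH-CBT, while the safety section rates serious adverse events and sets SAC-based procedures without naming an arm

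*Protocol article*

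**What the plan says.** Table 2 of the protocol article lists the SAC under adverse events, with no visit marked. Its timing is given by a footnote: "The SAC will be applied during the 8 weeks of NH-CBT in case of serious adverse events". The control intervention is not mentioned there.

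The section Data and Patients' Safety Monitoring describes the procedure. For serious adverse events, "the Severity Assessment Code (SAC) rating for adverse event reporting (33) will be completed by the therapist". It adds that "The study therapist has to contact the principal investigator", within 24 hours. For the upper two severity levels: "In the case of severe and major events (SAC 1 and 2), the trial would have to be suspended with immediate effect pending investigation". Events at SAC 3 and 4 go to the Data Safety and Monitoring Board for discussion. None of these sentences names an arm.

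The same section has the board decide on stopping for harm "based on their monitoring and evaluation of SAE attributed to our treatment". The Abstract gives the widest scope: "Adverse events will be monitored across all sessions".

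**The concern.** The assessment schedule and the safety section give different populations for the same form. The SAC level decides whether the suspension procedure or the board review is engaged, so an event without a grade has nothing to be matched against either.

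Control participants are exposed to comparable activity. Table 1 gives them the same range of movement retraining sessions as NH-CBT participants (2 to 23), and the safety section describes the risk of falls in this population without regard to arm. Serious events in the control arm are therefore a real possibility, and they are the natural benchmark for those under NH-CBT.

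Table 1 also trains each staff member in only one of the two interventions. If some staff worked from the table and others from the safety text, the difference in practice could follow the randomised arms. SAC-graded harms would then be collected differently by arm, which is the kind of difference that biases a comparison of harms.

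**Working it through.** There is no figure of the plan's to reproduce. The check is a comparison of the places that set the scope, with one line of arithmetic.

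**Scope by source (protocol article)**

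| Source | What it governs | Arm limit |
|---|---|---|
| Table 2, SAC footnote | When the SAC is applied | NH-CBT only |
| Safety section, therapist's rating | Who completes the SAC, and for what | None |
| Safety section, SAC 1 and 2 | Suspension of the trial | None |
| Safety section, SAC 3 and 4 | Board discussion | None stated, but framed by relation to the trialists' own treatment |
| Safety section, stopping for harm | Board's decision | Unclear (see step 3) |
| Abstract | Adverse event monitoring | None |

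**Step 1. Could NH-CBT be shorthand for both treatments?** Table 1 uses the name for the experimental arm only and calls the comparator supportive counseling and movement retraining. Where it means both, in the row on amount of treatment, it names both. The footnote's wording is therefore a restriction as it stands.

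**Step 2. When would a control participant come under the footnote?** Study Design and Procedure offers NH-CBT to controls who are not in remission at the 16-week follow-up. Read literally, the footnote would reach a control participant only in that delayed treatment, after the randomised comparison has ended.

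**Step 3. Does the board's criterion settle the scope?** It refers to events "based on their monitoring and evaluation of SAE attributed to our treatment". That could mean NH-CBT alone or either trial treatment, and the article does not say which.

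**Step 4. How many participants are affected?** Inputs: 172 planned (Sample Size, Power Calculations, and Interim Analyses) and 1:1 allocation in 8 blocks of 20 and 1 block of 12 (Methods for Minimizing Bias).

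- Planned total: 8 × 20 + 12 = 172.
- Control arm at full recruitment: 8 × 10 + 6 = 86.
- Share: 86 / 172 = 50%.

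Under the footnote, about 86 participants would be outside SAC grading during the 8 weeks of randomised treatment. Under the safety section, the number is 0. The article does not say which text prevails.

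**Step 5. Would another planned comparison fill the gap?** The Statistical Analysis section compares the Inventory for the Assessment of Negative Effects of Psychotherapy (INEP) between groups with t-tests and χ² tests. Table 2 schedules it at 8 weeks with no arm limit, so a randomised comparison of harms does exist. It covers negative effects of psychotherapy and does not grade serious events by severity. The article does not say that the board receives it.

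**The case against.** The best defence is that the footnote is a loosely worded table note and the safety section is the operative text. That section speaks of the whole trial population when it says "All trial participants will be assessed by a physiotherapist as they start the movement retraining part of the treatment". It refers to the study therapist generally, and elsewhere the article uses therapist for both arms. It suspends the trial as a whole. Followed as written, it rates control-arm serious events and applies the procedures to them.

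Much of this stands, and it limits the point. A reader might infer from the footnote that control-arm events are excluded from rating and have no route to suspension. The document does not support that, because the safety section states a route and names no arm. A reader might also infer that the trial has no randomised comparison of harms, but the INEP comparison is one. Nor does any text say that events in delayed NH-CBT would be pooled with those of the randomised period.

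The defence does not remove the conflict. The footnote is the only entry that gives the SAC's timing in the assessment schedule, nothing makes it subordinate to the safety section, and the safety section is itself unclear about whose treatment the board's criterion covers.

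**Conclusion.** This is an internal inconsistency to be corrected, not an established decision to leave controls unrated. As worded, the footnote is wrong or at odds with the safety section and the Abstract.

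The consequences are conditional on the footnote being followed. In that case, serious events in about 86 of 172 participants would have no SAC grade during randomised treatment, could not meet procedures defined by grade, and would provide no SAC-graded comparator for NH-CBT. The count assumes full recruitment at 1:1; if the trial stopped early, the share would still be about half. The article gives no serious event rate, so the number of events affected cannot be estimated. The primary efficacy analysis is untouched.

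**What to change.** Reword the Table 2 footnote to agree with Data and Patients' Safety Monitoring, so that SAC ratings are recorded in the same way in both randomised arms, over the same treatment period, and can be reported by randomised arm. Show any events during delayed NH-CBT separately.

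In the safety section, state whether the treatment in the board's harm criterion means NH-CBT alone or either trial intervention. The sponsor should also reconcile how the suspension and review procedures apply to each arm; which rule applies is for the sponsor to decide.

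The cost is one footnote and one or two sentences. Control therapists would complete a form already in use in the trial, and neither the sample size nor the efficacy analysis changes.
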